**Figure 2 F2:**
[figure not shown]
Schedule of enrolment, interventions and assessments.

### Economic evaluation

Information about a participant’s treatment (including recorded resource use of the surgical procedure if applicable), hospital stay, emergency department, outpatient, readmission and primary care attendances (if related to ongoing management of the fracture) and social care needs will be gathered through discussion with participants, as well as hospital and primary care databases. An assessment of total resource use will be made at baseline, week 12 and week 52 in order to inform an economic analysis between the two treatment groups.

Individual prices of these health resources will be based on information from national tariffs, such as the Unit Costs of Health and Social Care^51^ for primary care resources, NHS Reference Costs^52^ for secondary care resources and the British National Formulary (BNF)^53^ for prescriptions. If the price for a resource cannot be found from the references above, a suitable estimate will be identified from consultation with the hospital finance department. Prices will be estimated at 2018–2018 prices.

### Qualitative assessment

Using maximum variation sampling, up to 10 participants will be chosen to undertake a semistructured face-to-face interview 7–10 days after randomisation. An interview topic guide will explore their views on the trial and recruitment process, the presentation of study information, study documentation and reasons for agreeing to randomisation. A smaller selection of five participants who complete the trial will have another shorter follow-up interview at week 12. The aim will be to further explore their experience of the trial, data collection processes and overall perception of participating. Further specific consent for this qualitative interview nested study will be taken in addition to that agreed at the point of trial recruitment.

A number of clinicians will also be asked to partake in a semistructured interview to explore their experiences of the study. These interviews will consider participant recruitment (eligibility and randomisation) as well as the process of integrating the research with the clinical team. All participating clinicians will complete informed consent for interview, recording and transcription.

### Sample size calculation

This feasibility study will aim to provide estimates of recruitment and retention rates, and the variability of important outcomes, in order to generate appropriate power calculations for the definitive trial. It is estimated that sample sizes between 24 and 50 are required for a feasibility study.^54–57^ Therefore, we propose to recruit for a 10-month period, from which we expect to screen approximately 100 patients. Our estimates are based on data from Gateshead Health Foundation Trust, who screened 67 patients with a similar eligibility criterion over a 12-month period within a smaller acute trust catchment population.^17^ We assume in this feasibility study that 20% of patients screened are not eligible and a 60% recruitment rate, so we expect to recruit 48 participants. By recruiting 48 patients, the estimated recruitment rate has a SE of 5.5% (95% CI 48.4% to 70.8%). Given the short active follow-up period, we are allowing for a lower 10% 3-month attrition rate. This estimates that 43 participants will complete the study, thus estimating the 90% retention rate with a SE of 4.4% (95% CI 77.3%; 96.5%). Completed follow-up on 43 patients will allow an estimated SE for the TUG of 1.2 s assuming the SD is about 8 s (95% CI 6.6 to 10.2) and an SE of 0.9 for the RMDQ, assuming the SD is about 6 (95% CI 4.9 to 7.6).

### Data analysis

Data analysis will primarily be descriptive to address the aims of the feasibility study. A statistical analysis plan will be agreed prior to database lock and a CONSORT flow diagram produced. Data analysis overall will inform future trial feasibility and the hypothesis analysis plan for a definitive trial.

Characteristics of participants recruited will be summarised using appropriate descriptive statistics and compared with patients who were eligible but not randomised. Completeness of data collection will be reported by intervention group and overall.

Descriptive summaries of outcome data at each follow-up time point will be presented by intervention group and overall. Outcome distributions for suggested floor and ceiling effects will be checked. Confidence intervals will be presented for the proportion of patients consented, randomised and retained in the trial completing assessment at 12 weeks, both overall and by treatment group. Confidence intervals for the SD of the secondary outcomes will also be calculated where appropriate.

Exploratory analysis of continuous outcomes for the subsequent definitive trial will be performed to investigate potential treatment effects. Differences in mean values between baseline and 12 weeks will be presented, with 95% CI. This feasibility trial is not powered to perform hypotheses testing; however, descriptive statistics of the difference between randomised groups will inform the design of the main definitive trial. No subgroup analyses are planned, and no interim analyses will be performed aside from routine checks of safety data.

### Health economic analysis

The within-trial economic evaluation will determine the cost-effectiveness of the surgical intervention compared with non-surgical (standard) treatment from an NHS and Personal Social Services perspective. The evaluation will follow the reference case guidance for technology appraisals as set out by NICE.^58^ Effectiveness will be captured using quality adjusted life years (QALYs) as assessed by the EQ-5D-3L.^48^ The primary outcome of the evaluation will be the incremental cost-effectiveness ratio (ICER) per additional QALY (ICER) gained from surgical fixation compared with standard care. Sensitivity analyses will be performed to control for uncertainty, which will include one-way and two-way sensitivity analyses on (but not exclusively) age, gender and baseline scores, with a probabilistic sensitivity analysis to control for all uncertainty. Results of the sensitivity analyses will be presented as tornado plots, 95% CI for the ICER and cost-effectiveness acceptability curves.

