**Trial registration number:**

ISRCTN16719542; Pre-results.

Strengths and limitations of this studyDescriptive analysis on effectiveness of outcomes will inform hypothesis testing in a future definitive trial, including levels of variability in order to power the trial appropriately.Nested semistructured interview study will provide valuable qualitative data to inform future definitive trial acceptability and processes.Determines the feasibility of economic measures including detailed resource use collection and quality of life data within the two arms, to aid the design of more comprehensive economic evaluation in a future definitive trial.The intervention is a proven safe surgical intervention, already used in existing healthcare practice, but further safety data in this cohort of patients will also be collected.A pragmatic trial set in an existing healthcare setting that may lead to a number of limitations on trial processes, including recruitment, adherence to randomisation and ease of data collection.

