### Study design

The primary study design is a parallel, two-arm randomised controlled feasibility trial with participants allocated to either surgical or non-surgical intervention on a 1:1 ratio. A preliminary economic evaluation and a qualitative nested interview study will also be embedded within the feasibility study.

Participants will be recruited from a single site, Queens Medical Centre (QMC), Nottingham University Hospitals NHS Trust (NUH), a university teaching hospital serving a population of 700 000 and offering a tertiary spinal surgical unit.

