### Study procedures

Participant flow through the trial is summarised in figure 1. Face to face contact with participants and/or carer will be required at baseline (considered day 0), week 2 and a limited number of participants at week 12. Telephone interviews will be conducted with participants at week 4 and for the majority of participants at week 12. Week 12 marks end of trial for the participant, with further contact made at week 52 as part of the long-term safety analysis.

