## Discussion

The growing older person population confers a large group of potential patients with complex medical and social needs, both in terms of medical comorbidities, susceptibility to hospital acquired complications and dependency. With the numbers of PFFs set to exponentially increase in the coming years, the potential healthcare resource burden within this group of patients is alarming. A recent systematic review concluded that randomised controlled trials were required to develop evidence-based protocols to reduce morbidity and mortality in older people with PFF.^22 33 64^ Given that keyhole spinal sacral fixation is already an established treatment option with a sound safety record, we propose that surgical management should be considered earlier in the treatment of PFF in older people admitted to hospital. This is to maximise early pain management with the aim of preventing pain-related immobilisation and its short and long-term consequences.

In order to ensure that the outcome of a clinical trial in this area has a high level of validity, it must be delivered within the constraints of the existing healthcare service, where the burden of patient care falls. This feasibility trial, delivered within this existing healthcare service, will analyse the outcomes posed by some of these constraints, to ensure that a future definitive trial is able to answer the clinical question efficiently. The inclusion of an economic evaluation will also demonstrate whether surgical fixation offers value for money as well as clinical effectiveness, an important consideration for existing services.

Potential limitations of delivering a clinical trial of this kind within an active healthcare service include identification of the sacral fractures themselves. Any patient presenting with an anterior pelvic ring fracture would need to be referred for further imaging in order to identify sacral fractures and thus be considered within the eligibility criteria for this trial. However, as standard care for patients presenting with PFF is currently conservative care, clinicians may feel that further imaging would not change a patient’s treatment course and thus be an unnecessary expense. As an identified sacral fracture is a key requirement for the eligibility criteria, this clinician assessment may significantly affect recruitment.

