An area of confounding not specifically assessed in this feasibility trial is the possibility of variation in the usual care received by all participants in both groups. This is not set by the protocol and while minimised by using a single site setting, where staff are working from the same local guidelines, resources and practices, variation is likely inevitable due to the non-regimented workings of a real-world healthcare service. The effect of these innate differences could be further minimised by using analysis of variation in outcome measures from this feasibility trial in order to power a future definitive trial appropriately.

This study is not powered to test the hypotheses, but the data collected will be able to provide a descriptive analysis on effectiveness of outcomes in order to inform analysis in a future definitive trial. The key outcomes address questions posed by the possible limitations of conducting such a trial within an existing public health service, specifically to recruitment and adherence to randomisation. The future aim is that the feasibility trial will advise a valid and fully powered randomised controlled trial to test the hypothesis that surgical intervention in PFF is of clinical benefit to patients as well as being cost effective and safe.

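### The 95% CI promised for the ICER is probably not interpretable with about 43 completers, and the stated economic aim goes beyond a preliminary, unpowered evaluation

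*Protocol article*

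**What the plan says.** Under Health economic analysis, the ICER per QALY, with QALYs from the EQ-5D-3L, is the primary outcome of the evaluation. Uncertainty is to be shown in three ways: "Results of the sensitivity analyses will be presented as tornado plots, 95% CI for the ICER and cost-effectiveness acceptability curves".

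The purpose is described in two different ways.

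- As a finding on value. Health economic analysis: "The within-trial economic evaluation will determine the cost-effectiveness of the surgical intervention compared with non-surgical (standard) treatment". Discussion: "The inclusion of an economic evaluation will also demonstrate whether surgical fixation offers value for money as well as clinical effectiveness".
- As groundwork. Study design: "A preliminary economic evaluation and a qualitative nested interview study will also be embedded within the feasibility study". The strengths and limitations list, printed after the trial registration number: "Determines the feasibility of economic measures including detailed resource use collection and quality of life data within the two arms", in order to help design a fuller evaluation later. Discussion: "This study is not powered to test the hypotheses"; Data analysis says the same.

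On timing, the Economic evaluation section says: "An assessment of total resource use will be made at baseline, week 12 and week 52 in order to inform an economic analysis". Study procedures says: "Week 12 marks end of trial for the participant, with further contact made at week 52 as part of the long-term safety analysis". The abstract likewise treats week 52 as safety follow-up. Health economic analysis names no time horizon.

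**The concern.** The ICER divides incremental cost by incremental QALYs. If the data cannot separate the QALY difference from zero, the ratio passes through infinity within the range of plausible values and its 95% confidence set is not a finite interval. If the estimated QALY difference is negative, a given ICER value no longer has one meaning. A negative ratio can be surgery that is better and cheaper or surgery that is worse and dearer, and a positive ratio can be a gain at a price or a loss at a saving. With about 21 participants per arm followed for 12 weeks, this is a likely outcome rather than a remote one.

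The wording adds to the risk. A trial that says it will determine cost-effectiveness and demonstrate value for money invites readers to cite its ICER as an answer, although the design supports only a trial run of the economic methods.

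**Working it through.** **Inputs from the article (Sample size calculation; Randomisation).** About 100 screened, 80% eligible, 60% recruited, 10% attrition, 1:1 allocation.

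**Reproducing the article's figures.** Recruits: 100 × 0.8 × 0.6 = 48. Completers: 48 × 0.9 = 43.2, stated as 43, so about 21 to 22 per arm. The stated precision also reproduces:

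- recruitment SE √(0.6 × 0.4/80) = 5.5%, exact CI 48.4 to 70.8%;
- retention SE with 43/48 = 4.4%, exact CI 77.3 to 96.5%;
- TUG SE 8/√43 = 1.2 s;
- RMDQ SE 6/√43 = 0.9.

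The article gives no such figure for costs, QALYs or the ICER.

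**Assumptions.** The article gives neither a utility SD nor an expected utility difference. I took the SD of time-averaged EQ-5D utility as 0.15 to 0.30 and the true between-arm difference *d* as 0.05 to 0.15, over 12 weeks.

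**Condition for a bounded interval.** A Fieller-type 95% set for a ratio is a bounded interval only if the 95% CI of the denominator excludes zero. QALYs over 12 weeks equal mean utility × 12/52, so the test can be made on the utility scale.

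- SE = SD × √(2/21.5).
- Half-width = t(0.975, 41 df) × SE.
- P(CI includes zero) from the noncentral t with 41 df and noncentrality *d*/SE.
- P(estimate ≤ 0) = Φ(−*d*/SE).

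Example, SD 0.25: SE = 0.25 × 0.305 = 0.076. The half-width is 0.154 utility, or 0.154 × 12/52 = 0.036 QALY. The most that one arm can accrue at full health is 12/52 = 0.231 QALY.

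| SD | Half-width (utility) | P(CI includes 0): *d* = 0.05 | *d* = 0.10 | *d* = 0.15 | P(estimate ≤ 0): *d* = 0.05 | *d* = 0.10 |
|---|---|---|---|---|---|---|
| 0.15 | 0.09 | 81% | 43% | 11% | 14% | 1% |
| 0.20 | 0.12 | 87% | 64% | 33% | 21% | 5% |
| 0.25 | 0.15 | 90% | 75% | 52% | 26% | 10% |
| 0.30 | 0.19 | 92% | 81% | 64% | 29% | 14% |

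**Scale of the shortfall.** For an 80% chance that the QALY CI excludes zero (two-sided 5%), n per arm = 2 × (1.96 + 0.84)² × SD²/*d*². At *d* = 0.10 the total is 126, 198 or 284 for SD 0.20, 0.25 or 0.30. At *d* = 0.05 it is 504, 786 or 1132. The trial expects 43.

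**Possible further loss.** Study procedures restricts participants who lack capacity to clinically assessed questionnaires, and the Discussion puts cognitive impairment at up to 67%. The article does not say how many will lack EQ-5D data. If one third or two thirds of completers did (29 or 14 left), the chance of including zero at *d* = 0.10 and SD 0.25 would rise from 75% to 82% or 89%.

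**The case against.** Four objections deserve an answer.

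*The interval is not invalid.* A Fieller set keeps its coverage even when it is unbounded, and the article fixes no CI method. The probabilities above rest on assumed SDs and effects, and at the favourable corner only 11% of trials fail. This stands against any flat claim that the ICER interval cannot be interpreted. It does not help the reader who is given an unbounded set, which is the likely result over most of the assumed range.

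*Acceptability curves are also planned.* They remain valid when the QALY difference is near zero and should stay. They do not repair the interval promised beside them.

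*The article states the preliminary status several times, and its primary purpose is feasibility.* True, and this limits the harm. But the two stronger statements stand in the economic analysis section itself and in the Discussion, and an analysis plan that is not shown cannot remove a conflict in the published wording.

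*Two stronger readings go further than the text.*

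- A reader might infer that 52-week costs will be divided by 12-week QALYs. Nothing says so. The evaluation is described as within-trial, resource use is also assessed at week 12, so a matched analysis is possible, and the assessment schedule is in Figure 2, which was not available for this review. A mismatch is possible but not shown.
- A reader might also infer, because baseline scores appear among the sensitivity analyses, that QALYs will not be adjusted for baseline EQ-5D. That list is expressly not exhaustive, and covariates are commonly left to the statistical analysis plan.

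**Conclusion.** The concern holds on two counts.

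First, the promised 95% CI for the primary economic outcome is probably not interpretable at this size. The QALY interval would include zero in about 64 to 92% of trials for SD 0.20 to 0.30 and gain 0.05 to 0.10. At SD 0.15 the range is 43 to 81% for the same gains. The QALY estimate would be negative in about 5 to 29% of trials (SD 0.20 to 0.30). These figures depend on assumed utility SDs and effects and on all 43 completers contributing EQ-5D data. A large effect with a small SD would give a usable interval.

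Second, the verbs in Health economic analysis and the Discussion contradict the article's own description of the evaluation as preliminary and the trial as unpowered. That needs no assumption.

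The time horizon is a minor point to confirm, not an error. The feasibility aims are unaffected, but the change should be made before the economic results are analysed.

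**What to change.** 1. Report incremental costs and incremental QALYs separately, each with a 95% CI.
2. Replace the 95% CI for the ICER by incremental net monetary benefit, λ × ΔQALY − Δcost, with a 95% CI at stated values of willingness to pay λ. It is linear in both differences, so its interval is finite whatever the sign of ΔQALY. It will still be wide with 43 participants, and should be presented as such.
3. Keep the acceptability curves.
4. In Health economic analysis and the Discussion, replace *determine* and *demonstrate* with exploratory wording, such as exploring the feasibility of estimating cost-effectiveness.
5. State one common horizon for costs and QALYs, and say what role week-52 resource use has in the economic analysis.

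The cost is a few sentences in the protocol or analysis plan and a little extra analysis of data already being collected. No additional participants or visits are needed.

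### The planned 95% CI for the ICER may have no bounded or interpretable value if the QALY difference is not clearly different from zero; net benefit and separate cost and QALY intervals would serve better

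*Protocol article*

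**What the plan says.** The Health economic analysis section of the protocol article names the target: "The primary outcome of the evaluation will be the incremental cost-effectiveness ratio (ICER) per additional QALY (ICER) gained from surgical fixation". The denominator is fixed in the same section: "Effectiveness will be captured using quality adjusted life years (QALYs) as assessed by the EQ-5D-3L". One-way and two-way sensitivity analyses are planned, "with a probabilistic sensitivity analysis to control for all uncertainty". The displays are then listed: "Results of the sensitivity analyses will be presented as tornado plots, 95% CI for the ICER and cost-effectiveness acceptability curves".

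The article names no method for the ICER interval and does not say what happens if the QALY difference is near zero or negative. It does not mention net monetary benefit or the cost-effectiveness plane.

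On numbers, the Sample size calculation section says "This estimates that 43 participants will complete the study". The Data analysis section states that the trial is not powered for hypothesis testing and that a statistical analysis plan will be agreed before database lock. The Study design section describes the economic evaluation as preliminary.

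**The concern.** The ICER is the cost difference divided by the QALY difference. When the 95% CI of the QALY difference includes zero, the confidence set for the ratio is not an ordinary interval. It is either the whole real line or everything outside some range.

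Percentile limits from a bootstrap or a probabilistic analysis always give two finite numbers, but the ordering behind them is faulty. A dearer and better replicate has a positive ratio, and so does a cheaper and worse one. A negative ratio can mean that surgery dominates or that it is dominated.

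The choice of interval method can properly be left to an analysis plan, but no choice removes this difficulty. The quantity to be reported is already fixed in the article. At stake is whether the uncertainty shown for the primary economic outcome can be read by those designing and funding the definitive trial.

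**Working it through.** **The article's own figures.** Screening and recruitment: "we expect to screen approximately 100 patients" and "20% of patients screened are not eligible and a 60% recruitment rate, so we expect to recruit 48 participants". 100 × 0.80 × 0.60 = 48. With 10% attrition, 48 × 0.90 = 43.2, so 43 completers, as stated. At 1:1 this is about 21 and 22. The article gives no QALY SD, QALY difference or ICER to reproduce.

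**Assumed inputs (not in the article).** Utility SD 0.25 to 0.30; exchangeable within-person correlation r of 0.4 to 0.6; EQ-5D at weeks 0, 2, 4 and 12; a utility gain that starts at week 2 and is sustained to week 12.

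**Step 1: QALY weights.** The trapezium rule gives weights of 1, 2, 5 and 4 weeks, each divided by 52. A sustained gain g is worth (2 + 5 + 4)/52 × g = 0.2115 g.

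**Step 2: QALY SD.**
- Unadjusted: SD = (utility SD/52) × √[(1 − r) × 46 + r × 144], where 46 is the sum of squared weights and 144 = 12².
- Adjusted for baseline utility: subtract (1 + 11r)² inside the root.
- Smallest (SD 0.25, r = 0.6, adjusted): 0.25/52 × √(104.8 − 57.76) = 0.033.
- Largest (SD 0.30, r = 0.6, unadjusted): 0.30/52 × √104.8 = 0.059.

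**Step 3: SE of the QALY difference.** SD × √(1/21 + 1/22) = SD × 0.305, which gives 0.0101 to 0.0180.

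**Step 4: chance of no bounded interval.** The Fieller set is bounded only if the QALY difference differs from zero at the 5% level. The chance that it is not bounded is P(|Z| < 1.96) with Z ~ N(ΔQ/SE, 1). The chance of a wrong-sign QALY difference is Φ(−ΔQ/SE).

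| Utility gain | ΔQ | ΔQ/SE | No bounded interval | Wrong sign |
|---|---|---|---|---|
| 0.05 | 0.0106 | 0.59 to 1.05 | 82 to 91% | 15 to 28% |
| 0.10 | 0.0212 | 1.17 to 2.10 | 44 to 78% | 2 to 12% |
| 0.15 | 0.0317 | 1.76 to 3.15 | 12 to 58% | 0.1 to 4% |
| 0.20 | 0.0423 | 2.35 to 4.20 | 1 to 35% | 1% or less |

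**Step 5: a second route.** Take each person's mean utility over follow-up, with SD 0.15 to 0.35, and use the noncentral t with 41 df. The observed difference must exceed 2.02 × 0.305 × SD, which is 0.092 at SD 0.15, 0.154 at 0.25 and 0.216 at 0.35. The chance of a bounded interval is 7 to 19% for a true difference of 0.05, 15 to 57% for 0.10, 28 to 89% for 0.15 and 45 to 99% for 0.20. On this route a longer horizon scales the SD and the difference alike, so it does not change these chances.

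**Step 6: what would be printed.** Illustrative values: cost SD 6,000, utility SD 0.25, cost and QALY uncorrelated, 12 weeks.
- Cost difference 2,000, utility difference 0.05: the Fieller set is the whole real line. Simulated percentile limits are about −1.6 to +1.7 million per QALY, and 26% of draws have a negative QALY difference.
- Cost difference 2,000, utility difference 0.10: the whole real line again. Percentile limits are about −0.74 to +0.97 million, with 9.5% of draws negative.
- Cost difference 4,000, utility difference 0.10: the Fieller set is everything outside about −265,000 to +12,000.
- Cost difference 2,000, utility difference 0.20: bounded, at about −43,000 to +256,000.

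**The case against.** The strongest reply is that the plan already contains a sound display. The interval appears under the sensitivity analyses, beside tornado plots and acceptability curves, and the curves remain valid when the QALY difference is near zero. A reader might infer that the ICER interval is the sole error bar on the primary economic outcome. The text does not say so; it is one of three displays. This part of the reply stands and lowers the severity.

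A second reply is that the method is unstated and an analysis plan not shown here may handle it. This stands only in part. The unbounded-set probabilities are specific to Fieller, since percentile limits are always finite. But finite limits that pool opposite quadrants are no easier to interpret, and the article has already committed to the quantity.

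A reader might also infer that the interval would usually be meaningless. The documents do not support that as a general statement. They give no utility SD, correlation or expected effect, and at gains of 0.15 to 0.20 the interval is often bounded. Nor do the calculations support a fear that a narrow-looking interval would mislead: the illustrative percentile limits span more than a million per QALY and plainly signal great uncertainty.

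Last, this is a feasibility trial. The ICER is not among its feasibility outcomes, and the article ties no progression decision to the interval. That also stands.

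**Conclusion.** The point holds as a minor to moderate weakness in one of three planned displays. The ratio argument is general. How often it would matter in this trial depends on inputs that the article does not give.

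Under the assumptions above, failure to obtain a bounded interval is very likely for a sustained utility gain of 0.05 (82 to 91%), about as likely as not or worse for 0.10 (44 to 78%), possible for 0.15 (12 to 58%), and less likely for 0.20 (1 to 35%). The EQ-5D weeks and the 12-week horizon are also assumed: the Study procedures section ends the trial at week 12, while the Economic evaluation section collects resource use to week 52.

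Precision could be lower than computed. The Study procedures section limits participants without capacity to clinically assessed questionnaires. If the EQ-5D-3L is treated as self-reported, fewer than 43 people would contribute QALYs.

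**What to change.** In the Health economic analysis section, replace the 95% CI for the ICER with:

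- incremental cost and incremental QALYs, each with its own 95% CI;
- their joint distribution on the cost-effectiveness plane;
- incremental net monetary benefit, λΔQ − ΔC, with 95% CI at stated willingness-to-pay values λ. This is a difference and not a ratio, so its interval is bounded whatever the sign or size of ΔQ.

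Keep the planned acceptability curves. Report the point ICER when both differences have the same sign, and name the quadrant. This keeps the cheaper-and-less-effective case, where the ratio is still a real trade-off. State dominance when the signs differ.

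The cost is a change of wording and a few lines of code, using output that a bootstrap or the planned probabilistic analysis can supply. No extra data are needed and participants are unaffected. The downside is that readers get no interval on the familiar ratio.
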